**Fig. 3 Fig3:**
[figure not shown]
Analysis contrasts

We will conduct three exploratory analyses to guide design of the future hybrid effectiveness-implementation RCT. To inform primary outcome choice individual generalized linear mixed-effects regression models for longitudinal data (95%CI), controlled for blocking effect, will explore the effect of the 8-week program (IG T1-T0 versus DG T1-T0) on MVPA time, KOOS function in sport/recreation sub-scale, and KSES considering gender. To inform the most relevant muscle function outcome individual linear regression (95%CI) models, adjusted for age and sex, will compare the association between the change in knee extensor muscle function torque, power, and rate of force development over the 8-week intervention with the KOOS_4_. To inform optimal intervention length, a longitudinal mixed-effects model will examine the intervention effect at 18-weeks. This model will include the following fixed effects indicators: 1) study group (i.e., IG or DG) to account for baseline difference; 2) follow-up point (i.e., T1 or T2) to account for secular trend, and; 3) time since intervention initiation (i.e., 18- or 9-weeks) to estimate effects after these time intervals. The model will also include participant-specific random effects to account for repeated measures. As type II error is a greater concern in proof-of-concept trials than type I, we will not adjust for multiple comparisons [81].

Interview recordings will be transcribed verbatim and de-identified. Using a constant comparative approach [77] data will be coded and categories developed by comparing and determining meaningful patterns across codes. High-order themes will illuminate the relationship between categories. We will look for uniqueness in experience by gender. If gender-based themes are identified, data will be reanalyzed with a gender lens. Analysis credibility and trustworthiness will be fostered through data immersion, reflexive journaling, field notes, memoing and regular research team discussions of coding, early concepts and developing themes. A detailed audit of analytic decisions will be kept [82].

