**Methods:**

To assess the efficacy of a virtually-delivered, physiotherapist-guided exercise-based program (SOAR) to improve knee health in persons discharged from care after an activity-related knee injury, 70 people (16–35 years of age, 12–48 months post-injury) in Vancouver Canada will be recruited for a two-arm step-wedged assessor-blinded delayed-control randomized trial. Participants will be randomly allocated to receive the intervention immediately or after a 10-week delay. The program consists of 1) one-time Knee Camp (group education, 1:1 individualized exercise and activity goal-setting); 2) weekly individualized home-based exercise and activity program with tracking, and; 3) weekly 1:1 physiotherapy-guided action-planning with optional group exercise class. Outcomes will be measured at baseline, 9- (primary endpoint), and 18-weeks. The primary outcome is 9-week change in knee extension strength (normalized peak concentric torque; isokinetic dynamometer). Secondary outcomes include 9-week change in moderate-to-vigorous physical activity (accelerometer) and self-reported knee-related quality-of-life (Knee injury and OA Outcome Score subscale) and self-efficacy (Knee Self Efficacy Scale). Exploratory outcomes include 18-week change in primary and secondary outcomes, and 9- and 18- week change in other components of knee extensor and flexor muscle function, hop function, and self-reported symptoms, function, physical activity, social support, perceived self-care and kinesiophobia. Secondary study objectives will assess the feasibility of a future hybrid effectiveness-implementation trial protocol, determine the optimal intervention length, and explore stakeholder experiences.

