## Methods

### Aim

The primary objective of this study is to assess the efficacy of an 8-week SOAR program to improve knee extensor muscle strength, moderate-to-vigorous physical activity (MVPA), self-reported knee-related QoL, and knee-specific self-efficacy in people discharged from regular care after a sport or recreational-related knee trauma. Additional objectives are to evaluate the feasibility of a future hybrid effectiveness-implementation randomized controlled trial (RCT) protocol, determine the optimal intervention length, and explore stakeholder experiences.

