##### 9-week change in self-reported knee-related QoL

Patient partners identify QoL as the most relevant outcome and people with an activity-related knee injury face reduced QoL for up to 10-years [11]. The 5-item QoL subscale of the Knee Injury and Osteoarthritis Outcome Score (KOOS) questionnaire will be used to measure self-reported knee-related QoL. Each item is scored on an 0–10-point Likert scale, with 0 indicating no knee-related QoL and 10 indicating full knee-related QOL. Individual item scores are summed and transformed to a score out of 100 (0 representing poor knee-related QoL and 100 representing full knee-related QoL).

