##### 9-week change in self-reported knee-related pain, symptoms and function in sport and recreation

The 8-,18- and 5-item symptom, pain, function in sport and recreation subscales of the KOOS questionnaire will be used to measure self-reported knee-related pain, symptoms and function in sport and recreation [56]. Each item is scored on an 0–10-point Likert scale, with 0 indicating many symptoms and 10 indicating no symptoms. Individual item scores are summed to produce a total score. Higher scores indicate lower levels of knee-related pain and symptoms, and higher levels of knee-related sport and recreation function.

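### KOOS quality of life, a declared secondary outcome, is missing from the listed between-group models, while an exploratory KOOS subscale is included

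*Protocol article*

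**What the plan says.** **Outcomes declared.** In the protocol article, the Aim states the efficacy objective for knee extensor strength and for "moderate-to-vigorous physical activity (MVPA), self-reported knee-related QoL, and knee-specific self-efficacy". The Abstract (Methods) gives the secondary outcomes as 9-week change in MVPA and in "self-reported knee-related quality-of-life (Knee injury and OA Outcome Score subscale) and self-efficacy (Knee Self Efficacy Scale". Under Secondary outcomes the instrument is fixed: "The 5-item QoL subscale of the Knee Injury and Osteoarthritis Outcome Score (KOOS) questionnaire will be used to measure self-reported knee-related QoL". The same paragraph gives a reason for its importance: "Patient partners identify QoL as the most relevant outcome". Sport/recreation function appears later, after the Exploratory outcomes heading, under the title "9-week change in self-reported knee-related pain, symptoms and function in sport and recreation".

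**Analyses declared.** Statistical analyses says first that mean changes in every outcome will be described by study group, and by sex or gender. It commits to analysis as randomised, with multiple imputation. It then specifies a mixed-effects model for the primary outcome, knee extension torque. After Figure 3 it announces three exploratory analyses meant to help design the next trial. The first, intended to guide the choice of a future primary outcome, compares immediate and delayed groups over the first 9 weeks "on MVPA time, KOOS function in sport/recreation sub-scale, and KSES considering gender".

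**The concern.** The modelled outcomes look like the secondary outcome list with one member changed: MVPA and KSES are in both lists, but the KOOS subscale differs. An analyst following the text would fit no between-group model for QoL and would fit one for a subscale that the outcome section ranks lower.

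Two things are at stake. The objective of assessing efficacy on QoL would rest on group means alone, with no specified contrast and no interval to show how precisely the difference is known. And because the outcome and analysis sections name different KOOS subscales, either could later be presented as the planned one, and a reader could not tell from the article which had been intended.

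**Working it through.** The plan gives no figure on this point, so the check sets the two sets of statements side by side.

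**Step 1. Compare the lists for the 9-week comparison of immediate and delayed groups.**

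| Outcome | Status in Abstract, Aim and Outcomes | Between-group model in Statistical analyses |
|---|---|---|
| Knee extension torque | Primary; in the objective | Yes, as primary |
| MVPA | Secondary; in the objective | Yes, labelled exploratory |
| KSES | Secondary; in the objective | Yes, labelled exploratory |
| KOOS QoL | Secondary; in the objective | None named |
| KOOS sport/recreation | Exploratory | Yes, labelled exploratory |

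QoL is 1 of 3 secondary outcomes and 1 of 4 outcomes in the objective. It is the only one of those four without a named model.

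**Step 2. Look for any other analysis that would supply the QoL contrast.**

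- The description of mean changes covers all outcomes, QoL included. It gives means by arm, not a specified estimate of the difference with an interval.
- The intention-to-treat sentence says how participants are grouped. It specifies no model for any outcome.
- The regression on KOOS_4 relates change in muscle function to that score. It is an association analysis, not a comparison of randomised groups.
- The 18-week model names no outcome and serves the question of intervention length.

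None of these provides a planned 9-week between-group estimate and confidence interval for QoL.

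**Step 3. Check that a QoL model is feasible.** Procedures has participant outcomes evaluated at baseline, 9 weeks and 18 weeks, so the data needed are already in the plan.

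**Step 4. Check whether the sample size is touched.** It was set on torque alone: a difference of 0.22 Nm/kg, SD 0.25 Nm/kg, two-sided 5%, power 80%.

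n per group = 2 × (1.960 + 0.842)² × 0.25² / 0.22² = 2 × 7.85 × 0.0625 / 0.0484 ≈ 20.3, rounded up to 21, or 42 in total.

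This reproduces the article's 42 evaluable participants. QoL does not enter the calculation, so adding a QoL model changes nothing in it.

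**The case against.** The strongest reply is that the list after Figure 3 is not offered as the secondary-outcome analysis. It is introduced as exploratory work for a future trial, where a sport/recreation model has a purpose of its own, and an article may leave the secondary models to an analysis plan that is not shown. This has some force: it is a reason to keep the sport/recreation model. It does not remove the mismatch. The article names its models outcome by outcome, and two of the three after Figure 3 are declared secondary outcomes with no other 9-week between-group model. An analysis plan that followed this text would carry the gap forward, and one that modelled QoL would depart from the published list.

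Three stronger readings are tempting, and the documents do not support them.

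- **That QoL goes unanalysed.** A reader might infer this from the model list alone. Mean QoL change by randomised group is planned, and outcomes are to be compared as randomised. What is missing is a specified model and interval.
- **That outcomes have been switched.** The text does not say whether sport/recreation was substituted on purpose, entered by slip, or chosen for the future-trial question.
- **That the lack of multiplicity adjustment makes this worse.** The article declines adjustment for all comparisons and gives a reason suited to a proof-of-concept trial. That policy is separate from the QoL gap.

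**Conclusion.** The point holds as an internal inconsistency. The outcomes modelled at 9 weeks do not match the declared secondary outcomes. As written, KOOS QoL is reported only descriptively by group, an exploratory KOOS subscale is modelled, and two secondary outcomes are analysed under an exploratory label. The primary outcome, its contrasts and the sample size stand.

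This rests on reading the models named in Statistical analyses as the full set of planned 9-week between-group models. If a fuller plan already models QoL, the gap is one of wording in the article, but the two sections would still need to be reconciled.

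**What to change.** In Statistical analyses, add the KOOS QoL subscale to the 9-week mixed-effects models comparing immediate and delayed groups. Label MVPA, KOOS QoL and KSES as the secondary-outcome analyses. Keep the sport/recreation model and mark it as exploratory; it need not be removed.

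If sport/recreation was the intended secondary outcome, make the change in the other direction: revise the Abstract, the Aim and the Secondary outcomes section openly, give the reasons, and do so before unblinding.

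The first route needs a wording change and one more model on data already being collected. The number of outcomes with a 9-week between-group model rises from four (torque, MVPA, sport/recreation, KSES) to five. There is no extra visit or participant, and no change to the primary analysis.

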### Sample size

The sample size of knee injured participants is based on detecting a meaningful change in normalized peak knee extensor torque (Nm/kg) between study groups over 8-weeks, with 25% attrition. Bodkin et al. [44] reports that a gain in normalized knee extensor torque of 0.22 Nm/kg [44] discriminates people who achieve clinically relevant gains in self-reported knee function, 6–9 months post-trauma. To detect a mean change of 0.22 Nm/kg in the immediate intervention study group assuming no change in the delayed intervention study group, and a common standard deviation (0.25 Nm/kg), [11] a sample of 42 participants (21/group) is needed (two-sided test, 1-β = 0.8, α =0.05). Recruitment of 70 participants (35/group) allows for 25% attrition.

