### Statistical analyses

Descriptive statistics will be calculated for demographic and potential confounding variables (i.e., injury type, time since injury, prior or subsequent injury, prior treatment), and observed differences will be considered when interpreting findings, and during the design of a future hybrid effectiveness-implementation RCT. Randomization integrity will be monitored. Mean changes in all outcomes between T0 and T1, and T1 and T2 will be described by study group and sex (knee extension torque) or gender (physical activity, KOOS, KSES).

We will conduct intent-to-treat analyses (compare outcomes according to randomized study groups, regardless of intervention adherence). Missing outcome data due to missed visits or dropouts will be handled using multiple imputations of missing values. Generalized linear mixed-effects regression models for longitudinal data (95%CI), controlling for blocking effect, will estimate the effect of the 8-week intervention (IG T1-T0 versus DG T1-T0, and DG T2-T1 versus T1-T0) and delay (IG T1-T0 versus DG T2-T1) for the primary outcome (knee extension torque change; Fig. 3).

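### The exploratory model linking muscle-function change to KOOS_4 omits the starting KOOS_4 value and does not state its window, which costs precision and, if the arms are pooled over T0-T1, calls for a group term

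*Protocol article*

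**What the plan says.** The Statistical analyses section of the Protocol article introduces the analysis as one of several design aids: "We will conduct three exploratory analyses to guide design of the future hybrid effectiveness-implementation RCT". The second of these has the aim "To inform the most relevant muscle function outcome". Its method is a set of separate linear regressions that, "adjusted for age and sex, will compare the association between the change in knee extensor muscle function torque, power, and rate of force development". The predictors are therefore changes in muscle function, and they are related to KOOS_4 "over the 8-week intervention with the KOOS_4".

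Three things about the sentence matter:

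- Muscle function enters as a change. KOOS_4 is not called a change and has no time point.
- The adjustment set is stated and contains age and sex only.
- The window is the 8-week intervention. The Procedures section places that programme in weeks 1-8 for the immediate group (IG) and weeks 10-17 for the delayed group (DG). The sentence does not say whether each person's own programme period is used or T0-T1 in both arms.

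For the primary outcome, the same section names both kinds of comparison when it describes the "effect of the 8-week intervention (IG T1-T0 versus DG T1-T0, and DG T2-T1 versus T1-T0"), so the other text does not settle the window.

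The article does not define KOOS_4. I take it to be a composite of the four KOOS subscales listed under Outcomes (quality of life, pain, symptoms, sport and recreation). The Procedures section schedules outcomes at T0, T1 and T2, so a starting value exists for either window.

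**The concern.** Much of the spread in a follow-up KOOS_4 score reflects where each person began. In a regression on muscle-function change, that spread is residual noise unless the starting score is in the model. A real link between gaining strength and feeling better then becomes harder to see, in a section that itself gives type II error priority over type I.

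The second issue depends on the window. If treated IG and untreated DG changes over T0-T1 are put in one regression without a group term, a programme that moves both strength and KOOS_4 produces an association across the pooled sample even when none exists within either arm. A muscle measure could then look relevant because the programme shifted it, not because it tracks symptoms.

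At stake is the guidance this analysis gives on which muscle measure to carry into the next trial. The primary analysis is not affected.

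**Working it through.** **The plan's own figure first.** The Sample size section assumes a difference of 0.22 Nm/kg ("To detect a mean change of 0.22 Nm/kg in the immediate intervention study group assuming no change in the delayed intervention study group"), SD 0.25, two-sided α 0.05 and power 0.80:

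n per arm = 2 × (1.960 + 0.842)² × (0.25/0.22)² = 20.3, rounded up to 21, so 42 in total. This reproduces the stated number. It also gives the implied group shift in torque change: 0.22/0.25 = 0.88 SD. The article gives no sample size or power for the regression discussed here.

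**Inputs.** From the article: 70 recruited with 25% attrition, so 70 × 0.75 = 52.5, taken as 52; torque-change SD 0.25; group effect 0.22. N=70 is also shown because multiple imputation is planned. Assumed, because the article gives no values: correlation ρ between starting and follow-up KOOS_4 of 0.5, 0.7 or 0.8; partial correlation of 0.4 between torque change and follow-up KOOS_4 given starting KOOS_4; group effect on KOOS_4 of 0.3 or 0.5 SD.

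**Precision.** With KOOS_4 scaled to SD 1 and the starting score unrelated to torque change, the detectable correlation is:

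- follow-up level without starting value: 0.4 × √(1 − ρ²) = 0.346, 0.286, 0.240 for ρ = 0.5, 0.7, 0.8
- KOOS_4 change: 0.4 × √((1 + ρ)/2) = 0.346, 0.369, 0.379
- follow-up adjusted for starting value: 0.4 throughout

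Power from simulation (2,000 runs per setting, age and sex in every model):

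| N | ρ | Level | Change | Level adjusted for start |
|---|---|---|---|---|
| 52 | 0.5 | 0.71 | 0.70 | 0.82 |
| 52 | 0.7 | 0.52 | 0.75 | 0.82 |
| 52 | 0.8 | 0.38 | 0.79 | 0.82 |
| 70 | 0.5 | 0.84 | 0.84 | 0.93 |
| 70 | 0.7 | 0.67 | 0.88 | 0.93 |
| 70 | 0.8 | 0.50 | 0.89 | 0.92 |

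A Fisher-z check agrees. At N=52 and ρ = 0.7, atanh(0.286) × √47 = 2.02, and Φ(2.02 − 1.96) = 0.52. For the adjusted model, atanh(0.4) × √46 = 2.87, and Φ(2.87 − 1.96) = 0.82.

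**Group term.** Suppose there is no association within arms and both arms' T0-T1 data are pooled. With group effect g on KOOS_4, the correlation induced in the level model is (0.88 × g/4) / √[(1 + 0.88²/4)(1 + g²/4)]. For g = 0.5 this is 0.110/1.126 = 0.098; for g = 0.3 it is 0.060. Simulated false-positive rates at nominal 0.05, over all settings of N, ρ and g:

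| Model | False-positive rate |
|---|---|
| Level, age and sex | 0.06 to 0.13 |
| Plus starting KOOS_4, no group | 0.07 to 0.25 |
| Plus starting KOOS_4 and group | 0.04 to 0.06 |

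The second row is the worst because removing the starting-score noise makes the group shift larger relative to what remains. If every participant contributes only a programme period, the level model without group stays at 0.05 (N=52, ρ = 0.7, g = 0.5). Adding group to the adjusted model costs little power: 0.80 to 0.82 at N=52.

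**The case against.** The strongest reply is that this is one compressed sentence about an exploratory analysis, and that the form and time point of KOOS_4 belong in an analysis plan that is not shown. KOOS_4 change may well be meant: the same section says mean changes in all outcomes will be described. Most of the level-versus-change gap then disappears (0.70-0.79 at N=52 for change). On the window, the wording about the 8-week intervention can fairly be read as each person's own programme, in which case a missing group term does no harm.

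Much of this stands. A reader might infer that the analysis is underpowered. The article does not support that: it gives no power target, KOOS_4 SD or expected association, and under one assumption tried the literal model still reaches 0.84 at N=70. A reader might also infer that the plan definitely rejects KOOS_4 change, or that the result will reflect the group effect. The first is only the literal reading, and the second holds only under pooling over T0-T1. Nor does the article say that this analysis alone decides the next outcome, and misranking of the three measures is not quantified here.

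What the reply does not remove is that the adjustment set is stated, and it omits a starting value already collected. Adjusting for it did better than the change score as well as the level in every setting tried.

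**Conclusion.** The point holds as a low-severity, free improvement. The stated model lacks the starting KOOS_4 value, and the sentence leaves the KOOS_4 quantity and the window open. If a follow-up level is used, the relative loss of power is clear under all the assumptions tried: 0.38-0.71 against about 0.82 at N=52, and 0.50-0.84 against about 0.92 at N=70. The absolute values rest on the assumed partial correlation and the assumed KOOS_4 correlation over time.

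The group issue is conditional. It arises if treated and untreated T0-T1 changes are pooled, where false positives reach about 6-13% in the level model for an assumed KOOS_4 group effect of 0.3-0.5 SD. It does not arise if all changes come from programme periods. The two corrections belong together under pooling, because adding the starting score without group raises the rate to as much as 25%.

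**What to change.** Rewrite the sentence so that, for each muscle measure in turn, KOOS_4 at the end of the window is regressed on the standardised change in that measure, adjusted for KOOS_4 at the start of the same window, age and sex. Standardising puts the three coefficients on one scale for comparison.

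State the window as one of two options:

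- each participant's own programme period: T0-T1 for IG and T1-T2 for DG, with starting KOOS_4 at T0 and T1 respectively; or
- T0-T1 in both arms, with randomised group added as a covariate.

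The cost is one degree of freedom for starting KOOS_4 and a second if group is included. No new data or visits are needed.

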#### Primary outcome

##### 9-week change in normalized peak knee extension torque

Quadriceps weakness is an established independent risk factor for OA illness, [47] and deficits in quadriceps function persist for years beyond knee trauma [11, 48]. In a recent meta-analysis quadriceps weakness was associated with increased odds of symptomatic knee OA in women (OR 1.85, 95%CI 1.29,2.64) and men (1.43, 1.14,1.78) [49]. Isokinetic concentric and eccentric knee extension torque will be assessed on computerized dynamometer (Biodex, System 4™, Biodex Medical Systems Inc. USA) at 60 degrees/sec over 0–100 degrees [50]. The peak torque reached over 3 repetitions will be recorded and normalized to body mass (Nm/kg).

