##### 9-week change in normalized peak knee extensor and flexor rate of force development and power

Thigh muscle rate of force development and power have been overlooked components of muscle function, [48] despite compelling emerging evidence that they may be more strongly associated with knee function and symptoms early after injury [69–71] and in persons with OA [72]. Computerized dynamometer (Biodex, System 4™, Biodex Medical Systems Inc. USA) will be used to assess and calculate normalized knee extension and flexion rate of force development (Nm/s) and power (Watts). After completing the protocol for normalized peak concentric knee extension and flexion torque the participants’ knee joint will be fixed in 60 degrees of sagittal plane flexion. The peak values reached over three, 5 s repetitions will be recorded and normalized to body mass (Nm/kg).

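### The search for the most relevant muscle-function measure uses three separate regressions and gives no estimate, with uncertainty, of how the associations differ (minor)

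*Protocol article*

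**What the plan says.** The exploratory paragraph of the protocol article's Statistical analyses section (after Fig. 3) opens: "We will conduct three exploratory analyses to guide design of the future hybrid effectiveness-implementation RCT". The second of the three concerns muscle function. Its aim and method share one sentence: "To inform the most relevant muscle function outcome individual linear regression (95%CI) models, adjusted for age and sex", and these models "will compare the association between the change in knee extensor muscle function torque, power, and rate of force development over the 8-week intervention" with KOOS_4. The paragraph ends by ranking type II error above type I error for a proof-of-concept trial and stating that "we will not adjust for multiple comparisons".

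The predictors are defined under Outcomes. For knee extension torque: "The peak torque reached over 3 repetitions will be recorded and normalized to body mass (Nm/kg"). The section on rate of force development and power introduces "rate of force development (Nm/s) and power (Watts"), and later says that peak values are normalised to body mass, with the unit Nm/kg.

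The article states no common scale for the three changes, no joint model, and no estimate or interval for a difference between associations. It also states no rule for choosing a measure from the three results.

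**The concern.** The question is comparative: which change goes most closely with KOOS_4? The quantity that answers it is a difference between associations. An individual regression estimates one association, and its 95% CI describes the uncertainty of that slope alone.

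Two features stop the three outputs from being compared as they stand.

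- **Scale.** The slopes are KOOS_4 points per unit of torque, of power and of rate of force development. Their sizes depend on the units, so raw slopes cannot be ranked.
- **Dependence.** All three measures come from the same participants and the same dynamometer. The uncertainty of a difference depends on how strongly they correlate, and three separate CIs do not carry that information.

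A reader with three CIs may fall back on noting that one excludes zero and another does not, or on checking whether they overlap. Neither shows whether the associations differ. At stake is the choice of muscle-function measure for the next trial.

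**Working it through.** **The plan's own figure.** The only computed figure is the primary sample size: "a sample of 42 participants (21/group) is needed (two-sided test, 1-β = 0.8, α =0.05"). Per group, 2 × (1.960 + 0.842)² × 0.25² / 0.22² = 20.3, so 21 per group and 42 in all. It reproduces, but does not address this analysis, for which no figure is given.

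**Inputs.** From Sample size: 70 recruited and 25% attrition, so 70 × 0.75 = 52.5, taken as 52. If only the immediate group contributes, 35 × 0.75 = 26.25, taken as 26. With no loss, 70. Assumed, because the protocol gives none: the same true correlation r of each measure with KOOS_4, and a correlation k among the measures.

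**Step 1: what one CI does.** With intercept, age, sex and one muscle measure, df = n − 4. A slope's 95% CI excludes zero when its partial correlation exceeds t/√(t² + df). At n = 52, df = 48 and t = 2.011, so the threshold is 2.011/√(4.04 + 48) = 0.279. If all three true values are near 0.3, chance decides which estimates fall on which side.

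**Step 2: how often equal associations look different.** Simulated share of trials in which some CIs exclude zero and others do not, with k = 0.7:

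| True r (equal) | n = 26 | n = 52 | n = 70 |
|---|---|---|---|
| 0.2 | 23% | 32% | 37% |
| 0.3 | 34% | 40% | 34% |
| 0.4 | 41% | 23% | 13% |

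These are from 6,000 trials per cell. A separate run of 20,000 at n = 52 gave 33%, 38.5% and 25% in the same order, and 7% at r = 0.5. With no association at all (r = 0), the share at n = 52 is 10%. At r = 0.3 and n = 52 it is about 50% for k = 0.5 and 27% for k = 0.85.

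**Step 3: what a direct comparison gives.** By Williams' formula for two dependent correlations, with m = n − 2 for the two covariates, the standard error of the difference is

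√{[2((m − 1)/(m − 3))D + r²(1 − k)³] / [(m − 1)(1 + k)]}, where D = 1 − 2r² − k² + 2r²k.

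With r = 0.3, k = 0.7 and n = 52: m = 50 and D = 1 − 0.18 − 0.49 + 0.126 = 0.456. The numerator is 2 × (49/47) × 0.456 + 0.09 × 0.027 = 0.953, and the denominator 49 × 1.7 = 83.3. The standard error is √(0.953/83.3) = 0.107, so the 95% CI for a difference is about ±2.01 × 0.107 = ±0.22. In the simulation the average gap between the largest and smallest estimated partial correlation was 0.13 when the true gap was zero, well inside that width.

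Williams' test, applied to equal associations, finds at least one false difference in about 4% to 5% of trials with Bonferroni over three pairs, and in about 11% to 13% without.

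**Step 4: when a real difference exists.** With r = 0.5, 0.2 and 0.2, k = 0.7 and n = 52:

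- Non-overlap of the separate standardised CIs occurs in 3% of trials.
- At least one paired comparison rejects (Bonferroni) in 88%.
- The true best beats both rivals in 61% with Bonferroni and 78% without.
- Taking the largest standardised association picks the true best in over 99%.

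For smaller true differences (n = 52, k = 0.7):

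| True r | Largest standardised association is the true best | True best beats both rivals (Bonferroni) |
|---|---|---|
| 0.4, 0.2, 0.2 | 95% | 17% |
| 0.5, 0.35, 0.35 | 89% | 8% |
| 0.4, 0.3, 0.3 | 72% | 2% |

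Ranking on a common scale is therefore a good way to choose. What the plan lacks is that scale and a statement of how sure the ranking is.

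**The case against.** The strongest reply is that the article states no selection rule. It mentions no significance test, no requirement that CIs not overlap, and no ranking of raw slopes. A reader might infer that the trial will pick whichever measure reaches significance, or that its choice will be a matter of chance or units. The documents do not support that. The percentages in Step 2 describe a misreading that the wording leaves open, not a stated procedure. Step 4 shows that separate models on a common scale usually pick the right measure when one is better. If all three are equal, choosing any of them gives up nothing in association. This part of the reply stands.

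A reader might also infer that no measure should be preferred unless its paired interval excludes zero. That does not follow either. The analysis is exploratory, the protocol puts type II error first, and Step 4 shows that such a rule would usually return no choice.

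On units, the article's own labels for rate of force development and power are inconsistent, so part of the scale problem may be labelling. Body-mass normalisation would still leave three different physical quantities.

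Finally, a statistical analysis plan that is not shown could add a direct comparison, and individual models do not rule one out. But the article names the means by which it will compare, and those means as stated yield no difference. That much remains.

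**Conclusion.** The point holds as a minor one. The aim is comparative, and the method named for it gives three slopes in different units with separate CIs, so the stated comparison has no measure of uncertainty. Reading those CIs against zero would make three equal associations look different in roughly 25% to 40% of trials at n = 52 for r of 0.2 to 0.4, and in 7% at r = 0.5. All of this rests on an assumed correlation of 0.7 among the measures, on multivariate normal data, and on 52 participants contributing; Step 2 shows how the figure moves with each correlation and with n. The consequence is confined to an exploratory choice of muscle measure for the next trial. The primary efficacy analysis and the participants are unaffected.

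**What to change.** In the exploratory paragraph of Statistical analyses, keep the three models adjusted for age and sex, fitted in the same participants, and add that:

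1. each muscle-function change is expressed per SD, or the association is reported as a partial correlation;
2. the measures are ranked by that standardised association;
3. each pairwise difference in association is reported with a 95% CI, from a participant-level bootstrap or a Williams/Steiger method for dependent correlations, unadjusted for multiplicity as the protocol already states;
4. the intervals are used to say how well the data separate the measures; no difference is inferred from one CI excluding zero and another not, and significance is not required before a measure may be preferred.

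The cost is a few lines of wording and code, with no new data, visits or participants. The trial may have to report that the measures are not clearly separated. At n = 52, with an interval half-width near 0.22 under the assumptions above, that is a realistic outcome.
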